### Participation Procedure

All the candidates who accept to participate in the study are given information about the study, both verbally and by receiving an Information sheet. The candidates refusing participation are also asked to complete a quick survey (2 questions) to provide reasons for not participating. (see Figure 2)

### Control Group

The control group receives usual partner notification advice, and the health professional prints as many partner notification paper cards as the patient index case mentions to be able to provide partner notification paper cards to exposed partners. Therefore, exposed partners are expected to receive a partner notification paper card and a letter that are to be given to their health professional. The letter informs of the potential diagnosis and advised treatment. The card has information of the STI and the list of Sexual and Reproductive Health Centers and primary health care centers for sexual and reproductive health, where the recipient of the notification can go for diagnosis and potential treatment.

The random code given to the index case patient appears in the informed consent and in a short paper questionnaire (12 questions). Each 1 of the partner notification paper cards has a code in line with the study arm of the index case. This means that partners receiving a partner notification paper card from an index case assigned to the control arm are kept in the control arm themselves.

**Table 1 table1:** Sample size distribution for each primary health care center for sexual and reproductive health.

Location of health care centres^a^	Control^b^ N1	Intervention game^c^ N2	Intervention Web^d^ N3	Total N
Badalona	30	26	26	82
Sabadell	27	24	24	76
Granollers	27	24	24	74
Mollet	20	18	18	57
Mataró	20	17	17	55
Santa Coloma	14	13	13	40
Cerdanyola	12	11	11	34
Total	150	133	133	416

^a^Primary Health Care Centres for Sexual and Reproductive Health.

^b^Control group.

^c^Game intervention group.

^d^Web app direct intervention group.

**Figure 2 figure2:**
[figure not shown]
Algorithm of participation.STI: sexually transmitted infection.

### Web App Game Intervention Group

Individuals assigned to this group receive an Information sheet explaining the objectives and procedures of the study. After providing a signature of their informed consent, they receive a paper copy of this informed consent that has a specific code through which they enter the game by connecting to the *Notijoves* Web address. A paper card with the “Notijoves” Web address is given to the patients. Once they enter the Web app, they are asked to feed the given code into the field of Young PANDORA screen.

By entering the code, they start playing the game, and they are directed through different screens and situations. A Web-based questionnaire is inserted in the game. At the end of the game, they are also asked to respond to a satisfaction questionnaire.

The game is expected to motivate the youngster to notify partners of their exposure to an STI. While playing the game, the youngsters are asked to answer questions related to the clinical symptoms, prevention, and control of their recently diagnosed STI. Like this, they *learn by playing.* Another feature of the Web app is the link to advisory videos on how to approach the *face-to-face* notification of exposure to an STI. Finally, the game ends with a screen, where the youngsters can choose from among the different electronic tools to notify (short message service, email, or WhatsApp) either anonymously or by identifying themselves.

The electronic partner notification card has the following: (1) a code automatically assigned by the electronic system that is concordant with the arm where the index case patient entered the study, (2) the informative message advising the partner to visit a health center for diagnosis and potential treatment, and (3) a link to a list of health centers of the study and the Web app address, where the partner could go and where the informed partner could enter and participate in the study by introducing the code. Along with the notification card, the partner receives an electronic letter to be given to the health professional for him to be aware of the STI diagnosed to the sender of this notification and the advised treatment.

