### Aims and Objectives

The aim of this study is to describe the protocol for the randomized controlled trial of the *Notijoves* Web-based tool, adapted to smartphones for partner notification of STIs among youngsters aged 16 to 24 years.

The first objective of the study is to design the tool and evaluate its role in increasing partner notification done by the patient (patient referral partner notification) for all eligible sexual partners.

The specific objectives are the following:

Describe sociodemographic characteristics of index cases and consecutive sexual partnersDescribe coinfections within the groupDescribe acceptability, barriers, and preferences for executing partner notification using ICTsEvaluate the utility to apply the game theory (gamification to promote behavior change) in the design of a Web app for partner notification of STIsEvaluate the yield of ICTs for partner notification of STIs among sexual partnersAssess the impact of ICTs in primary transmission of STIsDescribe the characteristics of the social and sexual network among youngsters

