### Participants

This trial is being conducted in 7 public-based primary health care centers for sexual and reproductive health of Catalonia in the cities of Mataró, Badalona, Santa. Coloma de Gramanet, Granollers, Mollet, Cerdanyola-Ripollet, and Sabadell. Participants to the study are being recruited in each of the primary health care centers according to the following *inclusion criteria*: Young people 16 to 24 years old, diagnosed with at least 1 of the curable STIs (syphilis, gonococcus, or chlamydia). Partners who have had sexual contact within the previous 6 months since the diagnosis of index case.

*Exclusion criteria* are the following: diagnosis of other STIs (trichomonas, HIV, Hepatitis C, and Hepatitis B), which, although partner notification is advisable, will not be included to prevent complexity in the study. Under the diagnosis of 1 of these STIs, health professionals will perform according to the current clinical guidelines.

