### Main Outcome Variable

The main outcome variable of the study is the percentage of partners informed of their exposure to a STI from their index cases, according to the assigned study group.

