### Web App Direct Notification Intervention Group

Individuals assigned to this group receive an Information sheet explaining the objectives and procedures of the study. After providing a signature of their informed consent, they receive a paper copy of this informed consent that has a specific code through which they enter the *Notijoves* Web address. A paper card with the *Notijoves* Web address is given to the patients. Once they enter the Web app, they are asked to feed the given code into the field of Young PANDORA screen (see Figure 3). By entering the code, they are directed to a Web-based questionnaire and are offered an option to choose from among the different electronic tools (short message service, email, or WhatsApp) to notify either anonymously or by identifying themselves. Finally, they are also asked to respond to a satisfaction questionnaire.

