The questionnaire given to index cases collects data on the recruiting health care center, date of interview, date of birth, sex (boy, girl, transgender born as man, and transgender born as woman), country of birth, mother’s country of birth, education (without studies, primary studies, secondary studies, and university), with whom they have sex (boys, girls, or indistinctly boys or girls), number of sexual partners 6 months before the diagnosis, whether they look at webpages to obtain information about STIs (yes, no), whether they look for partners on the Web (yes, no), currently diagnosed with STI, positioning toward partner notification (will inform all partners, only some, none, and do not know), and reasons for not notifying.The questionnaire given to recipients of a partner notification card collects the same data as above and substitutes the last 3 questions with to which STI have you been exposed? How did you get to know your exposure (face to face, partner notification card, WhatsApp, short message service, email, and other)? Did you receive the notification anonymously (yes, no)?Those not wanting to participate are asked about their reasons in an open question. They are also recorded as index case or recipient of a notification.The opinion or satisfaction questionnaire collects data on whether the Web app helped its users to solve doubts related to STIs (not at all, a few, normal, quite a lot, and a lot), usefulness of the Web app to notify partners (not at all, a few, normal, quite a lot, and a lot), use of the anonymous option to notify (yes, no), easiness to choose from among the options to notify (yes, no, and if not, why not?), wish to recommend the Web app to friends (yes, no, and if not, why not?), and how can we improve the Web app? (open question)

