### Data Analysis

Descriptive analysis of index cases visiting health centers will be baselined to further assess differences in yield by groups. Chi-square test and Student *t* test for categorical and continuous variables will be used to assess differences in baseline characteristics among groups. Regression analysis and adjusting for confounding variables will be used to evaluate the primary outcome and relative risk, and its 95% CIs will be calculated. Significance will be set at .05. The multiple imputation method will be used to generate possible values for missing values. This is considered the gold standard for dealing with missing values. Data will be analyzed in Stata v12 (StataCorp LLC).

The methodology of analysis of the social and sexual networks will be used from an egocentric perspective. Structural measures of the network will be calculated, such as the size of the network, number of direct links, density, the geodesic average distance, diameter of ego’s network, and measures of centrality, such as the degree of intermediation of a contact or index case. Furthermore, we will compare social network, density, and structure. Network measurements will be done using the R statistical package.

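### In the web arms the only stated partner count is taken inside the app, so the primary outcome's denominator depends on using the intervention; in the control arm it does not

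*Protocol article*

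**What the plan says.** The section that defines the primary outcome states: "The main outcome variable of the study is the percentage of partners informed of their exposure to a STI from their index cases", compared by assigned group. The Participants section sets the partners in scope: "Partners who have had sexual contact within the previous 6 months since the diagnosis of index case".

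Under Data Collection, the questionnaire for index cases includes "number of sexual partners 6 months before the diagnosis", together with demographic items and the patient's intention to notify. How a patient reaches that questionnaire differs by arm:

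- Control Group: the random code "appears in the informed consent and in a short paper questionnaire (12 questions". The professional also prints notification cards to match the partners whom the patient mentions.
- Web App Direct Notification Intervention Group: "By entering the code, they are directed to a Web-based questionnaire".
- Web App Game Intervention Group: "A Web-based questionnaire is inserted in the game".

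In both web arms the patient is given a card with the web address and a code to type in. Data Collection says that the professional's entry triggers the allocation and records the diagnosed infection; it mentions no partner count. Data Analysis adds: "The multiple imputation method will be used to generate possible values for missing values".

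**The concern.** The outcome is a proportion of partners, so each index case needs a denominator. As described, a control patient can supply one whether or not they act on the advice to notify, whereas a web patient can supply one only by opening the intervention. Whether the denominator is missing is then tied to uptake in two arms and not in the third.

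Not opening the app plausibly goes with not notifying. If so, the web patients with usable data are a favourable selection, and a comparison with control could show a benefit that use of the app did not produce. The same form carries most of the covariates needed for the planned adjusted regression, so a non-user lacks the denominator and most adjustment variables together. The Limitations section does not mention this.

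**Working it through.** **1. Where a partner count can come from**

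| | Control | Direct web | Game |
|---|---|---|---|
| Form holding the partner number | paper, bearing the code | in the app, after code entry | within the game, after code entry |
| Other stated count | cards printed for partners mentioned | none | none |
| Recorded by the professional in any case | allocation, diagnosed infection | same | same |
| Count if the app is never opened | still obtainable | none stated | none stated |

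Centre and diagnosed infection are known for everyone without log-in. Partner number and the remaining questionnaire items are not.

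**2. The plan's own figures**

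Sample Size allows 10% withdrawal in each web arm and 20% in control, for at least 120 per group: 120/0.90 = 133.3 (stated 133), 120/0.80 = 150, and 133 + 133 + 150 = 416. These reproduce. The 10% is not said to cover non-login, and no log-in rate appears anywhere.

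If a share u of a web arm never logs in (assumed), the index cases with a stated denominator number 133(1 − u): about 120, 106, 93 and 80 at u = 10%, 20%, 30% and 40%.

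**3. Size of the bias if non-users are dropped or imputed as users**

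Let users notify a proportion a of partners and non-users b, with equal partner numbers per case. The rate in the arm as assigned is a(1 − u) + bu; the rate analysed is a. The overstatement is a − [a(1 − u) + bu] = (a − b)u.

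With a = 0.60 and b = 0.30 (both assumed):

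- u = 10%: 0.30 × 0.10 = 3 points
- u = 30%: 0.30 × 0.30 = 9 points
- u = 50%: 0.30 × 0.50 = 15 points

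Halving the gap to 0.15 halves these to 1.5, 4.5 and 7.5 points. With no gap the bias is zero.

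**4. The same mechanism when the arms are truly equal**

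Assume that 50% of partners are notified in every arm and that web non-users are dropped.

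- If non-users notify nobody, the observed web rate is 0.50/(1 − u): 0.556, 0.625, 0.714 and 0.833 at u = 10%, 20%, 30% and 40%. Against 0.50 in control, the spurious relative risks are 1.11, 1.25, 1.43 and 1.67.
- If non-users notify at half the overall rate, the observed rate is (0.50 − 0.25u)/(1 − u), and the relative risks are 1.06, 1.13, 1.21 and 1.33.

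In the first case, take each index case as one yes/no observation, 150 controls against 133(1 − u), and a two-sided level of 0.05/3 = 0.0167. The chance of a falsely significant result for one web arm is then about 7%, 34%, 83% and over 99%. This is a rough guide only, since a case may have several partners.

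**The case against.** A reader might infer that the web arms are cut down to compliers while control is analysed in full, so that the randomised comparison is broken and the web effect inflated. The article does not say that. It compares by assigned group, plans multiple imputation rather than deletion, and expects more withdrawals in control (20%) than in the web arms (10%). The net direction of all losses is therefore not established.

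Three other strong readings also fail. The loss is not of every covariate, because centre and diagnosed infection are known without log-in. Collection after allocation is not peculiar to the web arms, since the control form bears the random code and so also follows allocation. Nor is the partner number a post-treatment quantity: it concerns the six months before diagnosis, and late recording affects its reporting and completeness, not its nature.

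Some links are inferred. The article does not name the questionnaire item as the denominator, and the full protocol or analysis plan may define it. It does not say when or where the first log-in happens. The form records an interview date and the recruiting centre, so completion at the visit is possible, although handing over a web address points to later use. Figure 2, the participation algorithm, was not available to this review and might settle it. The imputation model is ordinary analysis-plan content, and the percentages above rest on assumed rates.

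What stands is narrower. No partner count independent of log-in is stated for the web arms, one is stated for control, and an analysis plan cannot restore a count that was never taken. Imputation for a non-user would have little beyond arm, centre and infection to work with.

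**Conclusion.** The concern holds in this form: in the web arms, having a partner count and most questionnaire covariates depends on using the intervention, and in the control arm it does not. If non-users notify less than users, dropping them or imputing their outcome from users pushes the web arms upward by the user/non-user gap times the non-login share. That is 3 to 15 points for an assumed 30-point gap and 10% to 50% non-login, and nothing if there is no gap or everyone logs in. The document gives neither quantity, so the size is unknown.

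The conclusion assumes that the questionnaire item supplies the denominator and that some web patients do not log in. It does not support a claim that the planned analysis excludes non-users, or that the overall bias is known to favour the web arms.

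**What to change.** Have every index case in all three arms complete the same short paper questionnaire at the clinic visit, including partners in the last six months, after signed consent and before the random code is generated. The article describes consent as printed and signed once the code has been drawn, so the signature must move ahead of the code; otherwise sexual-history data would be collected before consent.

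Use that count as the denominator in every arm, and keep all randomised index cases in the primary analysis by assigned arm. Count notifications under one rule that is identical across arms and does not depend on log-in or on an electronic code. Do not automatically score non-loggers as zero. A web patient who tells a partner face to face without opening the app generates no code, and the article says that partners arriving without one cannot be linked. Controls hold coded paper cards, so automatic zeros would bias against the web arms.

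The cost is a few minutes per patient and a reordered consent step; the 12-question form already exists. Patients recruited before the change (32 had accepted by early June 2018, with about 6 per month reported) keep the old capture mode and can be examined in a sensitivity analysis.

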### Web App Direct Notification Intervention Group

Individuals assigned to this group receive an Information sheet explaining the objectives and procedures of the study. After providing a signature of their informed consent, they receive a paper copy of this informed consent that has a specific code through which they enter the *Notijoves* Web address. A paper card with the *Notijoves* Web address is given to the patients. Once they enter the Web app, they are asked to feed the given code into the field of Young PANDORA screen (see Figure 3). By entering the code, they are directed to a Web-based questionnaire and are offered an option to choose from among the different electronic tools (short message service, email, or WhatsApp) to notify either anonymously or by identifying themselves. Finally, they are also asked to respond to a satisfaction questionnaire.

**Figure 3 figure3:**
[figure not shown]
Entrance to game “in Catalan”.

### What Happens to the Partners Receiving the Notification Card?

Partners visiting participating centers are easily linked to the study by their code, and they are also offered participation to the study. Once accepted, they also sign the informed consent, and they are asked to respond to a recipients’ questionnaire. After receiving the test results, if they are infected, they initiate the same procedure as an index case, with their given code, in concordance with the branch of the study that their index case was assigned. If they are not infected, the health professional registers results linked to the receptors questionnaire.

There may be partners visiting participating centers but not bringing the letter for the health professional and not having the code. These partners cannot be linked to any partner notification card, and therefore they are lost to follow-up for the system. Nevertheless, if they turn out to be infected, they are recruited as new index cases, with a new randomly assigned code. Moreover, those partners visiting a center out of the study area are lost to follow-up for the study.

### Data Collection

The Web app has 2 entries: the entry of health professional and the entry of the youngster.

The health professional entering the Web system activates the random assignment of the code to 1 of the 3 arms of the study and registers the information on the diagnosed STI.

The involvement of the youngsters with the study gives rise to different situations among candidates:

The index case wanting to participateThe recipient of the notification wanting to participateThe index case or the recipient not wanting to participateParticipants assigned to 1 of the intervention groups who finalized the experience of partner notification after using the Web app

For each 1 of the situations, there is a specific questionnaire:

The questionnaire given to index cases collects data on the recruiting health care center, date of interview, date of birth, sex (boy, girl, transgender born as man, and transgender born as woman), country of birth, mother’s country of birth, education (without studies, primary studies, secondary studies, and university), with whom they have sex (boys, girls, or indistinctly boys or girls), number of sexual partners 6 months before the diagnosis, whether they look at webpages to obtain information about STIs (yes, no), whether they look for partners on the Web (yes, no), currently diagnosed with STI, positioning toward partner notification (will inform all partners, only some, none, and do not know), and reasons for not notifying.The questionnaire given to recipients of a partner notification card collects the same data as above and substitutes the last 3 questions with to which STI have you been exposed? How did you get to know your exposure (face to face, partner notification card, WhatsApp, short message service, email, and other)? Did you receive the notification anonymously (yes, no)?Those not wanting to participate are asked about their reasons in an open question. They are also recorded as index case or recipient of a notification.The opinion or satisfaction questionnaire collects data on whether the Web app helped its users to solve doubts related to STIs (not at all, a few, normal, quite a lot, and a lot), usefulness of the Web app to notify partners (not at all, a few, normal, quite a lot, and a lot), use of the anonymous option to notify (yes, no), easiness to choose from among the options to notify (yes, no, and if not, why not?), wish to recommend the Web app to friends (yes, no, and if not, why not?), and how can we improve the Web app? (open question)

